## Abstract

**Background:**

Despite evidence that erythropoietin and intra- and postoperative blood salvage are expensive techniques considered to be non-cost-effective in primary elective total hip and knee arthroplasties in the Netherlands, Dutch medical professionals use them frequently to prevent the need for allogeneic transfusion. To actually change physicians’ practice, a tailored strategy aimed at barriers that hinder physicians in abandoning the use of erythropoietin and perioperative blood salvage was systematically developed. The study aims to examine the effectiveness, feasibility and costs of this tailored de-implementation strategy compared to a control strategy.

**Methods/Design:**

A cluster randomized controlled trial including an effect, process and economic evaluation will be conducted in a minimum of 20 Dutch hospitals. Randomisation takes place at hospital level. The hospitals in the intervention group will receive a tailored de-implementation strategy that consists of four components: interactive education, feedback in educational outreach visits, electronically sent reports on hospital performance (all aimed at orthopedic surgeons and anesthesiologists), and information letters or emails aimed at other involved professionals within the intervention hospital (transfusion committee, OR-personnel, pharmacists). The hospitals in the control group will receive a control strategy (*i.e*., passive dissemination of available evidence). Outcomes will be measured at patient level, using retrospective medical record review. This will be done in all hospitals at baseline and after completion of the intervention period. The primary outcome of the effect evaluation is the percentage of patients undergoing primary elective total hip or knee arthroplasty in which erythropoietin or perioperative blood salvage is applied. The actual exposure to the tailored strategy and users’ experiences will be assessed in the process evaluation. In the economic evaluation, the costs of the tailored strategy and the control strategy in relation to the difference in their effectiveness will be compared.

**Discussion:**

This study will show whether a systematically developed tailored strategy is more effective for de-implementation of non-cost-effective blood saving measures than the control strategy. This knowledge can be used in national and international initiatives to make healthcare more efficient. It also provides more generalized knowledge regarding de-implementation strategies.

**Trial registration:**

This trial is registered at the Dutch Trial Register NTR4044.

## Background

Total joint replacement surgery such as total hip arthroplasty (THA) and total knee arthroplasty (TKA) is associated with intra- and postoperative blood loss leading to postoperative anemia. This can be subsequently treated with allogeneic blood transfusion [1,2]. Yet, allogeneic blood transfusions carry the risk of infections and non-infectious transfusion reactions [3]. Therefore, different types of blood saving measures (BSMs) have been developed to reduce blood loss or to increase cell mass to avoid allogeneic transfusions [4].

Many studies on the effectiveness of the frequently used BSMs erythropoietin (EPO) and intra- and postoperative drainage and re-infusion of autologous blood (in short: perioperative blood salvage) in orthopedic surgery have been performed. Reviews and meta-analyses showed that EPO and perioperative blood salvage reduce transfusions. However, the included studies had several limitations such as a retrospective design, small patient numbers and poor methodologically quality leading to bias in favor of EPO and perioperative blood salvage [1,5-10]. When the costs of these techniques are considered, the use of EPO and perioperative blood salvage becomes controversial [8,11-17]. A large multicenter Randomized Controlled Trial (RCT) was recently performed to test the effectiveness and cost-effectiveness of EPO and perioperative blood salvage in elective THA and TKA [18,19]. It was shown that perioperative blood salvage in primary THA and TKA neither resulted in a decreased mean number of allogeneic blood units nor in a decrease in the proportion of transfused patients, and was more expensive due to the costs of the device and a prolonged hospital stay. EPO showed a significant decrease in the mean number of allogeneic blood units and proportion of transfused patients, but the costs of this technique were considered too high. It was thus concluded that EPO and perioperative blood salvage were not cost-effective in primary elective THA and TKA. For the use of EPO and perioperative blood salvage in revision THA and TKA no conclusions about the (cost-) effectiveness could be drawn [18,19]. These results are in line with recent literature. A number of trials that were not included in the currently available meta-analyses show that perioperative blood salvage is not superior to a regular drain or no drain in THA or TKA [20-24], other studies concerning the costs of EPO also doubt the cost-effectiveness in orthopedic surgery [11,14].

Despite the evidence, medical professionals keep using these BSMs in daily practice. Over 85% of Dutch hospitals frequently use EPO, perioperative blood salvage, or a combination of these in elective orthopaedic surgery [25]. This leads to unnecessary healthcare costs. So, to improve the efficiency of care delivery, a strategy is needed aimed at barriers and facilitators to stop using these non-cost-effective BSMs (de-implementation strategy) [26-29]. In the ‘Leiden Implementation Study of BlOod management in hip and knee Arthroplasties’ (LISBOA I) problem analysis study [30], such a strategy was developed in accordance with the implementation model of Grol [31]. This model, as with other theories of change, emphasizes that changes in current practice can only take place after the current barriers and facilitators for change have been identified and targeted. Therefore, prior inventory of barriers and facilitators incorporated in a tailored strategy can reduce the number of costly trials evaluating different implementation strategies [31-33]. The current study will test the hypothesis that the developed strategy is more effective for de-implementation of EPO and perioperative blood salvage in elective primary THA and TKA in comparison with a control strategy (*i.e*., passive dissemination of evidence).

### Objective

The ‘Leiden Implementation Study of BlOod management in hip and knee Arthroplasties, part two’ (LISBOA-II) aims to assess the effectiveness, feasibility and costs of a systematically developed tailored strategy for de-implementation of EPO and perioperative blood salvage in primary elective THA and TKA [30] compared to a control strategy in a cluster randomized trial.

## Methods

### Study design

A cluster randomized controlled trial including an effect-, process- and economic evaluation will be conducted in a minimum of 20 hospitals in the Netherlands using EPO and/or perioperative blood salvage in THA and TKA. Per hospital a representative orthopedic surgeon will be invited to participate in the study (see Additional file 1 for CONSORT checklist); consent of hospitals willing to participate will be gathered according to local hospital regulations. To prevent contamination bias, randomisation will take place at the hospital level stratified by geographic location of the hospitals. Randomisation will be performed by an independent researcher using a computer generated randomisation table concealed in a sealed envelope. The randomisation result will be revealed to the investigators and participating hospitals after the baseline measurement on effect outcomes takes place.

This trial compares:

1. The tailored strategy to de-implement use of EPO and perioperative blood salvage, and

2. A control strategy.

See Figure 1 for a flow-chart of the study design.

**Figure 1 F1:**
[figure not shown]
Flow-chart study design.

### Intervention

#### Tailored de-implementation strategy

The tailored de-implementation strategy in intervention hospitals is aimed at the barriers for de-implementation of non-cost-effective BSMs as identified in our problem analysis study, in which representative samples of orthopedic surgeons and anesthesiologists participated [30,34]. To ensure that we identified all relevant barriers, we used the Theoretical Domains Framework (TDF) [35-37]. The TDF includes 12 different domains derived from a large number of health psychology theories and their theoretical constructs. The main barriers to stop using non-cost-effective BSMs in elective orthopedic surgery were perceived by physicians within the following domains of the TDF:

1. Knowledge: lack of alternatives, lack of interest to gain additional information about stopping EPO and perioperative blood salvage.

2. Motivation & goals: lack of interest to save money for the society/ hospital, lack of benefit for the delivery of care.

3. Beliefs about consequences: pressure of suppliers to use BSMs, concerns about losing experience with the use of BSMs, concerns about the safety of patients when BSMs are stopped.

4. Social influences: the impact of blood management policy of other medical specialties/ blood transfusion committee, lack of influence of individual physician on blood management policy.

Barriers for EPO and perioperative blood salvage are largely similar and found within the same domains. Some barriers are more relevant for de-implementation of perioperative blood salvage (for example, concerns about losing experience with the use of BSMs) than for de-implementation of EPO. However, due to the large extent of overlap of barriers and the similar target groups, we developed a combined tailored strategy.

The developed tailored de-implementation strategy consists of four components carried out in a period of nine months. Every component targets one or more domains on which barriers have been identified [35].

1. Interactive education for orthopedic surgeons and anesthesiologists with a single visit in intervention month 1 (to target the domain: motivation & goals).

2. Feedback in educational outreach visits for orthopedic surgeons and anesthesiologists with a single visit in intervention months 5/6 (to target the domain: beliefs about consequences).

3. Dissemination of reports on hospital performance (BSM use and transfusion percentage) and comparison with hospitals that do not use EPO or perioperative blood salvage, *e.g*., ‘best practices,’ to orthopedic surgeons and anesthesiologists with two electronic newsletters sent in intervention months 4 to 6 and 7 to 9 (to target the domain: social influences).

4. Email with available evidence to other involved professionals, *e.g*., transfusion committee, OR-personnel, pharmacists with a single newsletter sent in intervention months 1 or 2 (to target the domains: knowledge, motivation and goals, and beliefs about consequences).

For the complete de-implementation strategy, see Figure 2.

**Figure 2 F2:**
[figure not shown]
**De-implementation strategy. **^1^Technique: the behavior change technique used to overcome the identified barrier. ^2^Mode: the way the technique will be delivered. ^3^Content: what will be delivered.

#### Control strategy

The control strategy consists of the passive dissemination of evidence via publication in scientific journals indexed for PubMed. No further actions to make the control hospitals aware of the published evidence will be undertaken. After the post-intervention measurement period, we will offer the control hospitals the possibility to have the interactive education as described for the intervention hospitals and a report on their hospital performance in comparison with best practices.

#### Study population

All types of hospitals (university hospitals, teaching hospitals, general hospitals and private clinics) that frequently use BSMs [25] will be invited to participate in this study. Further, we have previously shown that blood transfusion committees, hospital boards, patients, and other stakeholders are involved in blood management, but do not make decisions regarding the use of BSMs in THA and TKA [34]. Therefore, the de-implementation strategy will primarily be focused at orthopedic surgeons and anesthesiologists in the participating hospitals, with one strategy-component aimed at other involved professionals.

See Table 1 for in- and exclusion criteria for the participating hospitals and patients.

**Table 1 T1:** In- and exclusion criteria for participating hospitals and patients

**Inclusion criteria**	**Exclusion criteria**
Participating hospitals	
• Hospitals using EPO and/or blood salvage in patients undergoing primary elective THA or TKA on a regular basis (more frequently than in exceptional cases)	• Hospitals considering abandoning the use of EPO or blood salvage on their own initiative
• Hospitals performing at least 50 THA and/or TKA on average per 5 months	• Hospitals participating in trials that interfere with the use or the discontinuation of EPO or blood salvage
	• Hospitals employing the same group of orthopaedic surgeons or anaesthesiologists as a previously included hospital
Patients	
• Patients scheduled for primary elective THA or TKA	• Bilateral surgery
• Age >18 years	• Patients with a malignancy (except skin cancer or cured cancers)
	• A serious disorder of the coronary, peripheral and/or carotid arteries, a recent myocardial infarction or CVA (past 6 months)
	• Untreated hypertension (diastolic BP >95 mmHg)
	• Patients with a pregnancy
	• Patients with a coagulation disorder
	• Patients refusing or with a contraindication for allogeneic blood transfusions
	• Patients with untreated anaemia Hb <10 g/dl

#### Evaluation and outcome measures

1. Effect evaluation

The effect of the tailored strategy will be compared with the control strategy before and after carrying out the strategy. Outcomes will be measured at patient level, using retrospective medical record review at least three weeks postoperative with standardized registration forms. Measurement periods last for five months. Within each month, medical records of at least 10 consecutively treated patients will be reviewed in each participating hospital, with a maximum of 20 patients per month (depending on the number of patients treated within that month).

#### Primary outcome

The primary outcome is the % of patients undergoing primary elective total THA or TKA in which EPO or perioperative blood salvage is applied.

#### Secondary outcomes

Secondary outcomes are the patient outcomes of the surgery including: Post-operative hemoglobin (Hb) level, length of hospital stay and number of allogeneic red blood cell transfusions. Adverse events will also be registered: reactions on EPO use, transfusion reactions due to the use of perioperative blood salvage, transfusion reactions due to allogeneic transfusions and complications registered in patients’ medical records.

Other parameters measured in this study are patient characteristics (age, sex, BMI, ASA-classification, and pre-operative Hb), techniques used during the surgical procedure (type of anesthesia, use of tourniquet in TKA, surgical approach, use of other BSMs, use of drains) and postoperative care (postoperative blood loss, re-infusion of salvaged blood, type and length of postoperative anticoagulation).

2. Process evaluation

A process evaluation will be performed to assess the feasibility of the de-implementation strategy in comparison with the control strategy. Such an evaluation gives insight into the mechanisms and processes responsible for the effect of the de-implementation strategy and the control strategy [38]. The actual ‘exposure’ of clinicians to the elements of the de-implementation strategy, together with their experience with these elements, may influence the final results. At the end of the study period, experiences of clinicians with the elements of the de-implementation strategy will be measured using questionnaires, to further improve the de-implementation strategy for future use (if necessary). In these questionnaires, we will also ask about the presence and their awareness of barriers for behavior change.

Other local, non-study-related changes such as changes in staff, changes in blood management, changes in surgical techniques and local initiatives to optimize THA and TKA care will be registered in both study arms. See also Table 2.

3. Economic evaluation

**Table 2 T2:** Overview of measurements

	**Baseline measurements**		**Intervention period**		**Post-intervention measurements**	
	**Intervention**	**Control**	**Intervention**	**Control**	**Intervention**	**Control**
**On physician level**						
Barrier questionnaire					x	x
Process evaluation			x	x	x	
Resource use					x	x
**On patient level (through retrospective chart review)**						
Primary and secondary outcomes, complications and adverse events	x	x	x		x	x
Patient characteristics	x	x	x		x	x
Techniques during surgical procedure	x	x	x		x	x
Postoperative care	x	x	x		x	x

The economic evaluation will compare the costs of both de-implementation strategies in relation to their difference in effects. The analyses will not be performed separately for the de-implementation of EPO and perioperative blood salvage since it is impossible to determine which costs of the de-implementation strategy are exclusively made for the de-implementation of EPO and for the de-implementation of perioperative blood salvage. The economic evaluation will be performed from a healthcare perspective. No discounting will be applied due to the short time frame of the study.

The implementation costs concern the cost of execution of the de-implementation strategy [39], which consist of material costs (*e.g*., education material, information letter), and personnel cost (*e.g*., hours for the team of investigators conducting the strategy, hours of orthopedic surgeons and anesthesiologists attending the strategy-related activities). Resource use will be measured by questionnaires to the clinicians involved. For the valuation of the resource use, market prices (material) and wages including holiday allowance and social charges (personnel costs) are used [40].

Table 2 provides an overview of all measurements.

### Statistical analysis

All data will be entered and stored in an electronic database. Descriptive statistics include frequencies, percentages, medians, means and SDs. Hospital and patient characteristics of study hospitals will be compared using t-tests and non-parametric tests (Mann-Whitney U test) for continuous variables and χ^2^-test for proportions. The overall effect of the intervention will be evaluated by comparing the average outcome in the control hospitals with the average outcome in the intervention hospitals. The effects on the percentage of patients receiving a THA or TKA in which BSMs (stratified to the % patients with EPO and % patients with perioperative blood salvage) are applied will be adjusted for clustering of patients in hospitals. Therefore, multilevel logistic regression analysis will be performed. Analyses will be based on the intention to treat principle, meaning that all participating hospitals will be included in the study arm (control or intervention) to which they are originally assigned, regardless of whether they participated in the components of the tailored strategy.

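### Patient characteristics are to be compared with t, Mann-Whitney and chi-square tests that ignore hospital clustering, so their p-values will be too small wherever case mix varies by hospital

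*Protocol article*

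**What the plan says.** Under Study design, the article says that "randomisation will take place at the hospital level stratified by geographic location of the hospitals". The Sample size section allows for this with an ICC of 0.08 and 50 patients in each of 20 hospitals.

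The Statistical analysis section then makes three separate statements:

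- On characteristics: "Hospital and patient characteristics of study hospitals will be compared using t-tests and non-parametric tests (Mann-Whitney U test) for continuous variables", with a chi-square test for proportions. Clustering is not mentioned.
- On the effect in general: "The overall effect of the intervention will be evaluated by comparing the average outcome in the control hospitals with the average outcome in the intervention" arm. No test is named.
- On BSM use: "The effects on the percentage of patients receiving a THA or TKA in which BSMs" (split into EPO and perioperative blood salvage) "are applied will be adjusted for clustering of patients in hospitals". It continues: "Therefore, multilevel logistic regression analysis will be performed".

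The Secondary outcomes section lists the patient-level variables to be recorded, among them "patient characteristics (age, sex, BMI, ASA-classification, and pre-operative Hb". It also lists the secondary outcomes: "Post-operative hemoglobin (Hb) level, length of hospital stay and number of allogeneic red blood cell transfusions". No method is tied to these outcomes.

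**The concern.** The t-test, Mann-Whitney test and chi-square test assume independent observations. In a cluster-randomised trial, patients of one hospital always fall in the same arm. Any tendency of a hospital's patients to resemble each other therefore adds to the variance of the difference between arms, and these tests leave that variance out. The article allows for this in its sample size and in the analysis of BSM use, but names unadjusted tests for patient characteristics recorded from the same charts.

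All types of hospital are invited (university, teaching and general hospitals and private clinics), so some clustering of case mix is plausible. Characteristics are recorded in both arms at baseline and after the intervention. P-values that are too small could suggest a failed randomisation, or a shift in case mix between the arms, where ordinary variation between hospitals is explanation enough.

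**Working it through.** **Inputs from the article**

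- Two-sided alpha 0.05, power 80%, 50% against 30%, ICC 0.08 (for BSM use), 50 patients per hospital, 20 hospitals (Sample size).
- 10 to 20 charts per month for five months, that is 50 to 100 charts per hospital per measurement period (Evaluation and outcome measures).

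**Input not in the article**

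- The ICC of each patient characteristic. Values of 0.01, 0.02 and 0.05 are assumptions. The 0.08 is borrowed from BSM use and need not apply to age or BMI.

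**Step 1: the plan's own figure.** A comparison of 50% with 30% under individual randomisation needs 93 patients per arm (pooled variance, no continuity correction). The design effect is 1 + (50 − 1) × 0.08 = 4.92. Then 93 × 4.92 = 457.6 patients per arm, and 457.6 / 50 = 9.15 hospitals, rounded up to 10 per arm. That gives 20 hospitals and 1,000 patients, as stated. (An unpooled variance gives 18 hospitals and a continuity correction 22.) The plan thus reckons with a variance almost five times that of independent patients for BSM use.

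**Step 2: error of a test that ignores clustering.** With m charts per hospital, the design effect is DE = 1 + (m − 1) × ICC. The unadjusted standard error is too small by a factor √DE, so

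true type I error = 2 × [1 − Φ(1.96 / √DE)].

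Example with m = 50 and ICC 0.08: √4.92 = 2.218, 1.96 / 2.218 = 0.884, and the two-sided tail is 37.7%.

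| ICC | Source | DE, m = 50 | Error, m = 50 | DE, m = 100 | Error, m = 100 |
|---|---|---|---|---|---|
| 0.01 | assumed | 1.49 | 10.8% | 1.99 | 16.5% |
| 0.02 | assumed | 1.98 | 16.4% | 2.98 | 25.6% |
| 0.05 | assumed | 3.45 | 29.1% | 5.95 | 42.2% |
| 0.08 | stated for BSM use only | 4.92 | 37.7% | 8.92 | 51.2% |

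**Step 3: check by simulation.** With 10 hospitals per arm, equal hospital sizes and 8,000 runs, the t-test rejected in 10.7% and 16.5% of runs at ICC 0.01 (m = 50 and 100), 16.4% and 25.6% at 0.02, and 38.2% and 50.6% at 0.08. The chi-square test gave 11.0% and 16.0%, 17.1% and 24.7%, and 38.2% and 50.9%. The formula holds for this number of hospitals.

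**Step 4: what the figures cover.** They apply to characteristics measured on patients and compared between arms within one measurement period. For a characteristic of the hospital itself, the hospital is the observation, and patient clustering does not inflate the error.

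**The case against.** The strongest reply is that little depends on these tests. The primary analysis is multilevel and by intention to treat, and the article contains no rule that selects covariates from the p-values of a characteristics table. The sentence does not say outright that the comparison is between arms, and it also covers hospital characteristics, for which the tests are not faulty on this ground. All of this stands and limits the consequence. It does not remove the point: a comparison between arms is the natural reading, and the unadjusted tests are named in the text, so this is not a detail left to another document.

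Two stronger readings are tempting and are not supported.

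- A reader might infer that post-operative Hb, length of stay, transfusions and complications will also be tested without regard to clustering, because the adjustment is stated only for BSM use and the only model named is logistic. But the unadjusted tests are assigned to characteristics alone, and no method is named for the secondary outcomes. The general sentence on average outcomes can be read as a comparison of hospital averages, which would respect clustering. Stating an adjustment for one outcome does not exclude it for others, and a condensed article may leave those models to the full protocol or analysis plan.
- A reader might also take an error rate of, say, 16% to 50% as a fact about this trial. The lower figure needs an assumed ICC of 0.02. The upper one needs both the ICC for BSM use and the maximum of 100 charts in every hospital. As the ICC approaches zero, the error falls to 5%.

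**Conclusion.** The point holds for patient characteristics only. The article names tests that assume independent patients in a trial that randomises hospitals, and does so beside an analysis that it adjusts for clustering. Even at an assumed ICC of 0.01, the nominal 5% error at least doubles. Larger values follow from the table and are conditional on the ICC, on equal hospital sizes and on 50 to 100 charts per hospital. The article's only ICC belongs to a different variable, so no single row can be taken as the figure for this trial.

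The harm is misleading evidence of imbalance in case mix. It is not a false-positive finding on BSM use: the primary analysis stands. For the secondary outcomes there is a matter to confirm, not an error shown.

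**What to change.** Replace the sentence on characteristics. Describe patient characteristics by arm and measurement period, without significance tests. If tests are kept, use methods that account for clustering: a model with a random hospital effect, or a comparison of hospital-level summaries. Keep hospital characteristics as a separate item, with the hospital as the unit.

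In the same revision, confirm that post-operative Hb, length of stay, transfusions and complications will also be adjusted for hospital clustering, each with a model suited to its scale.

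The cost is a few lines of text and, if the adjustment is not already planned, a few additional mixed models. No change to data collection, sample size or the primary analysis is needed.

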### Sample size

We expect to detect an absolute difference of at least 20% in BSM use between the group receiving the de-implementation strategy and the control group. We assume that frequent BSM use, as assessed in the Dutch survey [25], means that BSMs are applied in 50% of the patients. To detect a difference of 20% (from 50% to 30%), with alpha 0.05, a two-sided testing and power of 80%, an intra-cluster-correlation coefficient of 0.08, 50 patients per hospital and 20 hospitals are needed (total of 1,000 patients). Given the 70% of hospitals in The Netherlands frequently applying BSMs [25], this means that 69 hospitals are eligible for the present study. Since the average hospital performs about 550 total hip and knee arthroplasties per year, it is feasible to include 20 hospitals and at least 50 patients per hospital in 5 months, before and after the intervention period.

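### The planned effect analysis does not say how the baseline BSM use measured in every hospital enters the model; adjusting for it would gain precision at almost no cost

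*Protocol article*

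**What the plan says.** Two places in the protocol article describe the effect comparison, and they do not match.

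- Evaluation and outcome measures, effect evaluation: "The effect of the tailored strategy will be compared with the control strategy before and after carrying out the strategy". Each measurement period lasts five months with 10 to 20 charts per hospital per month, so at least 5 x 10 = 50 charts per hospital per period. The Abstract and Table 2 confirm that the primary outcome is collected in both arms at baseline and again afterwards.
- Statistical analysis: the overall effect is evaluated by "comparing the average outcome in the control hospitals with the average outcome in the intervention hospitals". The percentages with EPO and with blood salvage "will be adjusted for clustering of patients in hospitals", by multilevel logistic regression. No baseline covariate, period term or arm-by-period term is named.

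The Sample size section is a two-arm, single-period calculation (50% v 30%, "an intra-cluster-correlation coefficient of 0.08", 50 patients in each of 20 hospitals) with no baseline term. Under Study design, "randomisation will take place at the hospital level stratified by geographic location of the hospitals"; baseline BSM use is not a stratification factor.

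**The concern.** A before-and-after comparison and a comparison of arm averages are different estimators with different standard errors, and the text does not say which is primary. An analyst who follows the Statistical analysis section alone would leave the baseline charts out of the effect estimate.

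That matters more than usual here. There may be only about 20 randomised units. All hospital types are eligible, and Table 1 asks only that use exceed exceptional cases, so baseline use can vary widely. The randomisation does not balance it. A hospital's earlier use is a natural predictor of its later use.

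Timing adds to this. Trial status reports that baseline collection ended in January 2014 and that the intervention was under way in March 2014. Baseline imbalance could therefore already be known while the role of baseline in the model was still open.

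**Working it through.** **Inputs from the Sample size section:** 50% v 30%, two-sided alpha 0.05, power 80%, ICC 0.08, m = 50 patients per hospital, 20 hospitals.

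**Assumptions, not in the document:** 1:1 allocation (10 hospitals per arm); the same ICC in both periods; a between-period correlation c of true hospital levels of 0.5 to 0.9, equal in both arms. Calculations are approximations on the percentage scale.

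**1. The plan's own figure.** Two proportions without continuity correction need 93 patients per arm. The design effect is 1 + 49 x 0.08 = 4.92. Then 93 x 4.92 = 457.6 per arm, and 457.6/50 = 9.15 hospitals, rounded up to 10. That gives 20 hospitals and 1,000 patients, as stated. For this design:

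- SE = sqrt((0.25 + 0.21) x 4.92/500) = 0.0673
- Power = Phi(0.20/0.0673 - 1.96) = Phi(1.01) = 84%
- With a pooled null variance it is 83.4%, and with a t reference on 18 df 80.3%. All meet 80%.

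**2. Chance imbalance at baseline (p = 0.5).**

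- Between-hospital variance = 0.08 x 0.25 = 0.02; within-hospital variance = 0.92 x 0.25 = 0.23
- SD of the arm difference = sqrt((2/10) x (0.02 + 0.23/50)) = sqrt(0.00492) = 0.070, or 7.0 points
- P(gap above 10 points) = 2 x (1 - Phi(10/7.01)) = 15%

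Ten points is half of the 20-point target.

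**3. Gain from baseline adjustment.** The correlation between a hospital's two observed percentages is r = c x m x ICC/(1 + (m - 1) x ICC) = c x 4/4.92 = 0.813c. Adjustment multiplies the variance by 1 - r^2.

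| c | r | 1 - r^2 | Power, normal | Power, t on 17 df |
|---|---|---|---|---|
| 0 | 0 | 1.000 | 84% | 80.0% |
| 0.5 | 0.41 | 0.835 | 90% | 86.5% |
| 0.7 | 0.57 | 0.676 | 95% | 92.6% |
| 0.9 | 0.73 | 0.465 | 99% | 98.4% |

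The variance falls by about 17% to 54%. The difference detectable with 80% power is (1.96 + 0.84) x 0.0673 = 18.8 points unadjusted. It becomes 18.8 x sqrt(0.835) = 17.2 points at c = 0.5 and 18.8 x sqrt(0.465) = 12.8 points at c = 0.9. Given an observed 10-point baseline gap, the expected carry-over into the unadjusted later difference is 10r, about 4 to 7 points.

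**4. If both periods are modelled with a hospital intercept only.** The hospital-by-period variance 0.02(1 - c) is then left in the patient-level residual. The ratio of true to model variance is (0.02(1 - c) + 0.0046)/((0.23 + 0.02(1 - c))/50), and the type I error is 2 x (1 - Phi(1.96/sqrt(ratio))).

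| c | Ratio | Type I error |
|---|---|---|
| 0.5 | 0.0146/0.00480 = 3.04 | 26% |
| 0.7 | 0.0106/0.00472 = 2.25 | 19% |
| 0.9 | 0.0066/0.00464 = 1.42 | 10% |

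**The case against.** The best defence is that the article is condensed. The Statistical analysis section is silent on baseline and does not exclude it, and a full protocol or SAP may specify covariates and random effects. The phrase about average outcomes is a general description; the sentences after it specify multilevel logistic regression on patients, not a bare test of hospital means. This stands, and it limits the point to what the article does state: two descriptions of the effect comparison that do not fit together, one of which names an estimator and an adjustment without baseline.

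Second, hospitals are randomised. A reader might infer from the 15% figure that chance imbalance biases the trial or leaves it underpowered. The documents do not support that. The imbalance is ordinary sampling variation already carried by the cluster-adjusted standard error and by the sample size, which reproduces. What is lost is efficiency, and protection against an estimate that misleads given the imbalance actually seen.

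Third, the gain rests on a correlation that the document does not give, applied equally to both arms. If some hospitals abandon these measures outright, as the strategy intends and as the Discussion fears for fast-track programmes, baseline will predict later use less well, particularly in the intervention arm. This also stands: the 0.5 to 0.9 range is illustrative. The downside is small, however. At zero correlation the lost degree of freedom costs 0.3 points of power (80.3% to 80.0%).

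**Conclusion.** The point holds as an improvement that costs almost nothing, not as an error that must be corrected for the trial to be valid. The Evaluation and Statistical analysis sections do not agree on the role of baseline, and the analysis text as written leaves unused a measurement taken in every hospital. Baseline imbalance of 7.0 points (SD) follows from the plan's own inputs and 10 hospitals per arm. The variance reduction of about 17% to 54%, and the rise in power from about 84% to 90-99%, also depend on the assumed correlation.

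A reader might go further and infer that the planned test has a type I error of 10% to 26%. That figure belongs only to a two-period model with a hospital intercept and no hospital-by-period effect, which the article does not specify. It is a warning about one way of reconciling the two sections, not a defect of the stated analysis.

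**What to change.** Reconcile the two sections and state, before post-intervention data are seen, that the primary model is a multilevel logistic regression of post-intervention BSM use on arm, with a random hospital effect, adjusted for each hospital's baseline percentage of BSM use. For the separate EPO and blood salvage analyses, use the matching baseline percentage.

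If both periods are to be modelled together instead, include a random hospital-by-period effect as well as the random hospital effect. The two models are not equivalent, because they treat sampling error in the baseline percentage differently, so one should be named as primary.

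The cost is a change of wording and one degree of freedom. The baseline data are already collected, and neither the number of hospitals nor the chart review changes.
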